### Data analysis

Database will be established using Epidata 3.0, and statistical analysis will be performed using SPSS 18.0. This trial uses differential testing; a *p*-value less than 0.05 will be considered statistically significant, and the confidence intervals for the parameters will be estimated as 95%.

In this trial, validity analysis based on MITT (modified intention to treat) analysis will be conducted. The primary and secondary outcomes will be analyzed with both MITT and PP (per protocol) analysis. Conclusion of MITT analysis will be the primary analytical method, and if the conclusions of PP analysis and MITT analysis are consistent, the credibility of the conclusions can be improved. SP (safety population) analysis will be used to analyze laboratory evaluations, adverse events, and adverse reaction data. SP will be defined as the denominator for the incidence of adverse reactions.

Descriptive statistics will be used to systematically describe primary and secondary outcomes. Means, standard deviations, and confidence intervals will be presented based on data from the control group and intervention groups. Frequency distributions, percentages, medians, and mean rank order will be presented based on quantitative data and rank data. Positive rates, positive number, and total number of retrieved LNs will be presented based on qualitative data. The number of events, number of missingness, median survival time, and survival rate will be presented based on survival data. Efficacy analysis will be performed on data following descriptive statistics. This study utilizes Pearson chi-square test for qualitative data, *t* test for quantitative data, Wilcoxon rank sum test for ranked data, Log-rank test for univariate analysis and Cox regression model for multivariate analysis of survival data, and two-tailed test for safety indicators and incidence of adverse reactions.

Abnormal values will be judged when the observed value is greater than P75 or less than P25, and 3 times more than the interquartile range defined as P75 subtracts P25. Sensitivity analysis will be performed on the abnormal data, and the data will be retained if results are not contradictory. If there is a contradiction, specific analysis will be conducted.

Subgroup analysis will be performed to identify risk factors for the prognosis according to the specific circumstances of the data.

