#### Withdrawal criteria

The following are the withdrawal criteria: (1) diagnosis of M1 during or after surgery, i.e., distant metastasis upon intraoperative exploration or postoperative pathology, or positive exfoliated cells in the abdominal cavity; (2) duodenum invasion of diagnosis of T4b during or after surgery; (3) incomplete D2 dissection or R0 resection owing to masses formed by regional LNs coalescing or vital vessel surrounding; (4) necessary additional surgery during operation; (5) serious perioperative complications (unable to tolerate surgery or anesthesia); (6) referring to emergent surgery due to condition changes judged by attending physicians; (7) voluntary withdrawal or discontinued treatment due to personal reasons at any stage; (8) treatment violates study protocol.

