### Outcome

The primary outcome is the total number of retrieved LNs. The secondary outcomes include positive rate, false positive rate, negative rate, false negative rate, number of metastatic LNs, rate of LN metastasis, relationship between LN metastasis and dual staining, morbidity and mortality, 3-year disease-free survival rate, 3-year overall survival rate, 3-year recurrence rate, postoperative recovery, duration of surgery, changes in body weight, intraoperative blood loss, intraoperative mortality, incision length, body temperature, and changes in lab parameters (albumin, prealbumin, hemoglobin, white blood cells, C-reactive protein, etc.).

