### Intervention

#### Preoperative administration of CNs

Following enrollment, surgery should be performed within 2 weeks (including day 14). In addition to routine preoperative management, peritumoral submucosal CNs injection is administered 1 day before surgery in CNs group and dual tracer group. Carbon nanoparticles suspension injection (Chongqing Lummy Pharmaceutical Co., Ltd.) is diluted into 25 mg/ml with saline and then injected using “sandwich method.” Briefly, approximately 0.5 ml saline is firstly injected into the submucosal layer for mucosal elevation. Then, 0.2 ml CNs is injected. Finally, 0.5 ml saline is injected again to prevent leakage of CNs. This injection is performed at both proximal and distal sides of tumor under gastroscopy.

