#### Interim analysis

Safety interim analysis and futility interim analysis will be conducted every 8 months, and analysis report will be submitted to the Efficacy and Safety Evaluation Committee. The specific contents of the report include the following: ineligible patients/potentially ineligible patients, reasons for end of treatment/discontinuation/study protocol, adverse events and serious adverse events, completion rate of laparoscopic surgery, proportion of conversion to laparotomy, enrolled protocol deviations, disease-free rate/disease-overall survival rate of all participants, etc. The Efficacy and Safety Evaluation Committee will review and discuss the report in accordance with the procedures documented in the Clinical Safety Information Management Guidelines and make written recommendations to the study director including whether to continue the enrollment of the study.

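### Morbidity, mortality and laboratory outcomes are assigned both to MITT/PP and to the safety population with no rule on which leads, and some post-enrolment removal rules overlap with morbidity

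*Protocol article*

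**What the plan says.** The Outcome section places safety endpoints among the secondary outcomes: "relationship between LN metastasis and dual staining, morbidity and mortality, 3-year disease-free survival rate", and later intraoperative mortality, body temperature and "changes in lab parameters (albumin, prealbumin, hemoglobin, white blood cells, C-reactive protein, etc".

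The Data analysis section then makes two assignments in one paragraph:

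- "The primary and secondary outcomes will be analyzed with both MITT and PP (per protocol) analysis", with the hierarchy "Conclusion of MITT analysis will be the primary analytical method".
- "SP (safety population) analysis will be used to analyze laboratory evaluations, adverse events, and adverse reaction data". SP is named as the denominator for adverse reactions only.

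Three sections remove participants after enrolment for reasons that can be safety events or follow from them:

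- Withdrawal criteria: item 4 (additional surgery needed during the operation), item 5 ("serious perioperative complications (unable to tolerate surgery or anesthesia") and item 6 (emergent surgery after a change in condition, judged by the attending physician).
- Exclusion criteria: item 15, conversion to laparotomy, which can be known only at surgery.
- Date management (data handling): participants with missing data are withdrawn from the study, without imputation.

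The Interim analysis section asks for "completion rate of laparoscopic surgery, proportion of conversion to laparotomy", and Surgical parameters records conversion and its reason.

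**The concern.** A postoperative complication is both morbidity, a secondary outcome, and an adverse event. A fall in albumin is both a laboratory change, also a secondary outcome, and a laboratory evaluation. Each can be reported twice with different denominators, and the one general statement of hierarchy favours MITT.

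This matters because the sets may differ through the outcome itself. When a removal reason is a complication, or a consequence of one, taking the patient out deletes the event from the numerator and the patient from the denominator. The Discussion paragraph of the Abstract gives safety of dual tracing as an aim alongside efficacy, so it should be settled in advance which complication rate answers that aim.

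**Working it through.** **1. The plan's own figure.** The only relevant number is the group size. A one-sided two-sample t test with d = 3/8.6, alpha 0.05 and power 0.80 needs 102.30 per group, hence 103. Then 103/0.8 = 128.75, hence 129, and 4 × 129 = 516. The Sample size section reproduces. It says nothing about complications, and the document gives no rate of complications or withdrawals by cause or by arm.

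**2. The assignments side by side.**

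| Data | Set as a secondary outcome | Set under the SP sentence | Which leads? |
|---|---|---|---|
| Laboratory changes | MITT and PP | SP, named explicitly | not stated |
| Morbidity | MITT and PP | SP, as adverse events | not stated |
| Mortality, intraoperative mortality | MITT and PP | SP, as adverse events | not stated |
| Body temperature | MITT and PP | SP only if counted as an adverse event | not stated |
| Adverse reactions | – | SP, also fixed as denominator | SP |

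Only the last row is settled.

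**3. Which removal reasons overlap with the endpoints.** Withdrawal items 4 to 6 and conversion overlap with morbidity. Item 5 is narrow: its parenthesis limits it to patients who cannot tolerate surgery or anaesthesia, whereas Postoperative parameters defines a serious complication as Clavien-Dindo grade III or above. Death, temperature and laboratory change are not removal reasons. They can lead to removal only indirectly, through the missing-data rule.

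**4. Size of the understatement, if removed patients leave the set.** Let p be the true risk and w the share of patients with an event who are removed. Then

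observed risk = p(1 − w) / (1 − pw).

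Every p and w below is an assumption. For p = 6% and w = 50% with 129 per arm: 129 × 0.06 = 7.74 events, 3.87 removed and 3.87 left, and 3.87/(129 − 3.87) = 3.1%.

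| True risk p | w = 25% | w = 50% |
|---|---|---|
| 5% | 3.8% | 2.6% |
| 10% | 7.7% | 5.3% |
| 15% | 11.7% | 8.1% |

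**5. Effect on a comparison of two arms.**

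- Equal risk (10% and 10%) and equal removal: the difference stays 0.
- Equal risk of 10%, removal 25% against 50%: 7.7% − 5.3% = 2.4 points of spurious difference, in either direction.
- True 10% against 15%, equal removal: the 5.0-point difference shrinks to 4.0 points (w = 25%) or 2.8 points (w = 50%).

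Equal removal thus creates no false difference, but it can shrink a real one.

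**The case against.** The strongest reply is that safety is already covered. SP takes laboratory, adverse event and adverse reaction data, and safety indicators have their own two-tailed test. A bleed or perforation from the carbon nanoparticle (CNs) injection is an adverse event and would be counted in SP, so a reader who infers that such harms are lost goes too far. This stands and limits the consequence. It does not say which result leads for morbidity and mortality, where the only general hierarchy names MITT.

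A second reply is that no text says withdrawn patients leave MITT, and that membership rules are commonly left to the full protocol or analysis plan. That also stands: understatement in MITT is conditional, and the missing definition is not itself the point. The point is the double assignment, which is stated in the article. Removal from PP is the natural reading, and withdrawal from the study for missing data suggests that some patients would not be analysed.

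A third reply is that the removal rules apply to all four arms. A reader might infer bias in favour of the tracer arms, because "peritumoral submucosal CNs injection is administered 1 day before surgery in CNs group and dual tracer group" and the trial is open-label. Those facts make unequal removal possible. The documents give no frequency that would show it, and the direction is open.

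Finally, a reader might infer that the reported conversion proportion must be zero because conversion is an exclusion. It need not be. Conversion is recorded, is not a listed outcome, and is requested in a monitoring report that nothing restricts to MITT.

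**Conclusion.** The contradiction holds: the same safety data are assigned to MITT/PP and to SP, and no rule says which leads. The overlap of withdrawal items 4 to 6, conversion and the missing-data rule with morbidity gives the choice of set a practical consequence.

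The size cannot be fixed from the document. If removed patients leave the set, a true 6% with half of the events removed appears as about 3.1%. Both values are assumptions, and a smaller removed share gives a smaller effect. If removed patients stay in MITT, MITT has no such bias and only the missing lead rule and the PP version remain.

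The stronger statement, that the MITT comparison is too favourable and unequal between arms, is not supported. It needs a membership rule and arm-specific removal rates that the document does not give. This should be corrected before analysis, but it does not affect the sample size or the primary outcome.

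**What to change.** In Data analysis:

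1. Limit the sentence on secondary outcomes in MITT and PP to the efficacy outcomes.
2. Name SP as the lead set for morbidity, mortality, intraoperative death, body temperature and laboratory outcomes. MITT and PP versions may be shown as supportive.
3. Define SP as every randomised participant in whom a study procedure began (the CNs gastroscopy or anaesthesia for gastrectomy, whichever came first), kept in regardless of later exclusion, conversion, withdrawal or missing data.

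Also reconcile exclusion item 15 with the Interim analysis section by counting conversions in that same set.

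The cost is a few sentences. Surgical parameters and Postoperative parameters already provide for recording complications, laboratory values, temperature and conversion, and the sample size does not change. The downside is that reported complication rates may be slightly less favourable.

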### Sample size

This study is a superiority testing trial (one-tailed trial) of which the primary outcome is the number of retrieved LNs and study subjects will be divided into 4 groups. Combined with our previous findings and literature reports, the standard deviation σ of the total number of LNs in control group was 8.6 [9, 13, 17]. The *α* (test level) is set as 0.05 and power (1-β) is 0.8. A difference of more than 3 in the total number of detected LNs will be considered as significant, i.e., the effect value *d* = 3/*σ* = 0.35. Thus, at least 103 (102.3) participants are required in each group. Considering an expected dropout rate of 20%, 129 (128.75) participants are finally required in each group, leading to a total of 516 participants.

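### The data-class rule files the total node count with qualitative data for chi-square, at odds with the mean-based sample size, and its natural reading tests node-level rates as if nodes within a patient were independent

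*Protocol article*

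**What the plan says.** The Outcome section is clear about the endpoint: "The primary outcome is the total number of retrieved LNs". The Sample size section treats it as a measurement with a spread, "the standard deviation σ of the total number of LNs in control group was 8.6", and sets the target as a difference between groups: "A difference of more than 3 in the total number of detected LNs will be considered as significant".

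The Data analysis section sorts outcomes by data class. Its descriptive part states: "Positive rates, positive number, and total number of retrieved LNs will be presented based on qualitative data". Later in the same paragraph, tests are assigned by class: "This study utilizes Pearson chi-square test for qualitative data, *t* test for quantitative data, Wilcoxon rank sum test for ranked data". No sentence names a test for the primary outcome by itself.

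The node-related secondary outcomes are in the Outcome section: "The secondary outcomes include positive rate, false positive rate, negative rate, false negative rate, number of metastatic LNs, rate of LN metastasis", followed by the relationship between metastasis and dual staining. The article does not say whether these rates are computed per node or per patient, and it mentions no method for several nodes from one patient.

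**The concern.** There are two problems, of different weight.

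**Primary outcome.** Applied literally, the class rule sends the total node count to Pearson chi-square, while the sample size rests on comparing patient means. An analyst working only from this text would find the primary endpoint under the wrong heading.

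**Node-level rates.** The classifying sentence groups a rate with a positive count and a total, which looks like a numerator and denominator counted in nodes. Whether a node is stained or metastatic is a property of that node, and chi-square is the only test named for qualitative data. Pearson chi-square assumes independent observations. Nodes from one patient share a tumour, an injection procedure and a metastatic state. If nodes are pooled across patients and compared between arms, the standard errors will be too small and differences between arms will be declared too often. This matters for the trial's rationale, because the Discussion gives a lower false-negative rate as a possible benefit of dual tracing over ICG alone.

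**Working it through.** **1. Reproduce the sample size.** Inputs from the Sample size section: difference 3, SD 8.6, one-sided α 0.05, power 0.80.

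- d = 3/8.6 = 0.349.
- Normal approximation: n = 2 × ((1.645 + 0.842)/0.349)² = 101.6 per group.
- Exact one-sided two-sample t test (noncentral t): n = 102.30 per group, the article's own decimal.
- Dropout: 103/0.8 = 128.75, so 129; 4 × 129 = 516.

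The plan's figure is therefore a t-test calculation on per-patient counts.

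**2. Between-arm rates over all retrieved nodes.** The article gives neither the mean node count nor the intra-patient correlation (ICC). Assumed: 35 nodes per patient, 103 patients per arm, ICC 0.05 to 0.30, no true difference.

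- Design effect: DEFF = 1 + (35 − 1) × ICC.
- Real type I error of a nominal 5% pooled test: 2 × (1 − Φ(1.96/√DEFF)).

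| ICC | DEFF | √DEFF | Type I error |
|---|---|---|---|
| 0.05 | 2.7 | 1.6 | 23% |
| 0.10 | 4.4 | 2.1 | 35% |
| 0.20 | 7.8 | 2.8 | 48% |
| 0.30 | 11.2 | 3.3 | 56% |

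The √DEFF column is the factor by which the true standard error exceeds the reported one. Varying the mean from 20 to 40 nodes (SD 8.6) gives about 18 to 26% at ICC 0.05 and 48 to 59% at ICC 0.30. Beta-binomial simulation of two arms with 15% positivity agrees with these figures and returns about 5% at ICC 0.

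**3. False-negative rates.** On the usual definition only metastatic nodes enter, so clusters are smaller and node-negative patients contribute nothing. Assumed: 55% of 103 patients node-positive (about 57 per arm), with a mean of 5 metastatic nodes when positive and a skewed (geometric) distribution, hence variance 20.

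- Effective cluster size = E[m²]/E[m] = (20 + 25)/5 = 9.
- DEFF = 1 + (9 − 1) × ICC = 1.4, 1.8 and 3.4 at ICC 0.05, 0.10 and 0.30.
- Type I error = 10%, 14% and 29%. Simulation agrees.

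If every node-positive patient had exactly 5 metastatic nodes, DEFF = 1 + 4 × ICC = 1.2 to 2.2 and the error would be about 7 to 19%. The skew matters, but inflation remains.

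**4. Staining against metastasis.** Here stained and unstained nodes are compared within the same patients, so the between-arm design effect does not apply. If each patient has a similar stained share (an assumption), simulation of the pooled chi-square gave about 4%, 3% and 2% at ICC 0.05, 0.10 and 0.30, which is slightly conservative. If staining varies strongly between patients, the error can go the other way. No single figure is defensible.

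**The case against.** The strongest reply is that the classifying sentence concerns presentation, not testing. It can be read as naming a rate with its numerator and denominator. The same paragraph promises means, standard deviations and confidence intervals for the groups and gives the t test for quantitative data, and a per-patient count with an SD is quantitative. Chi-square would not be a sensible comparison of one count per patient. A reader might infer that the plan holds two rival analyses of its primary outcome; the documents do not support that. This part of the objection stands: the label is most likely a slip. The text still needs correcting, because its own rule, followed literally, reaches the wrong test.

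The second reply is that nothing in the article says nodes will be pooled. Per-patient proportions would be quantitative and go to the t test, and a condensed article may leave the unit of analysis to a fuller document. It is true that pooling is an inference, so one cannot say that the plan declares nodes independent. But the article does fix a test for this class of data, and the classifying sentence points to counting in nodes. That rule is what needs repair, not the missing detail.

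A reader might also carry the 23 to 56% over to every node-related outcome. That fails: the range assumes all retrieved nodes compared between arms. It is too large for false-negative rates and may have the wrong direction for staining against metastasis.

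**Conclusion.** The point holds in two parts. First, the primary outcome's name is listed under qualitative data, which read literally conflicts with a sample size that is demonstrably a t-test calculation. This is probably a drafting error, and it has no effect on the 516 participants. Second, the natural reading of the class rule is chi-square on pooled nodes, which ignores within-patient correlation. If that is what is done, nominal 5% becomes about 23 to 56% for between-arm rates over all retrieved nodes and about 10 to 29% for false-negative rates, with no figure for staining against metastasis.

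These sizes rest on assumed ICCs (0.05 to 0.30), node counts and node-positive share, none of which the article gives. The clustering problem concerns secondary outcomes only. Confidence is firm on the wording and on the existence of some inflation if nodes are pooled between arms, and moderate on its size. The change should be made, but the issue does not threaten the primary comparison if the t test is what is meant.

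**What to change.** In the Data analysis section:

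- State that the primary outcome is the number of retrieved nodes per patient, a quantitative variable compared between groups on means with a 95% CI. Keep the node total in the qualitative sentence only as the denominator of the rates, and say so.
- State the unit of analysis and the denominator of each rate.
- Replace Pearson chi-square for node-level rates, and for staining against metastasis, with a method clustered on the patient: GEE, a mixed logistic model or a patient-cluster bootstrap of the pooled rate. Per-patient proportions are an alternative. If they are used for the false-negative rate, say how patients without metastatic nodes are handled, since they have no such proportion.

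The cost is a few sentences, plus a check that the chosen method is available in the software the plan names. The sample size stays at 103 per group, 129 with dropout and 516 in total, because it already rests on a t test. Intervals for between-arm rates will usually be wider. No clinical procedure changes; node-level records linked to the patient are needed, which the planned staining outcomes already imply.

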## Introduction

Lymph node (LN) metastasis is the most common mode of metastasis in gastric cancer. Even in early gastric cancer, the rate of LN metastasis is about 2–20% [1]. Numerous studies have shown a close correlation between number of dissected LNs and accuracy of postoperative pathological staging and long-term prognosis [2, 3]. However, it is a great challenge for surgeons to identify LNs from hypertrophic adipose tissue or complex lymphoid tissue without increasing the risk of surgery and postoperative complications. Therefore, improving intraoperative visualization of LNs becomes an urgent clinical issue [4].

In recent years, navigation technique using tracers such as indocyanine green (ICG) and carbon nanoparticles (CNs) to visualize LNs has been proved to be effective for sentinel LN tracing and dissection in breast cancer, lung cancer, and other tumors [5–10]. Also, it has been confirmed that either ICG or CNs can assist surgeons to dissect LNs in laparoscopic gastrectomy. Nevertheless, there are still limitations in the application of two tracers.

ICG administration includes multi-point subserosal injection and peritumor submucosal injection [9, 11–13]. Subserosal injection of ICG can help to obtain better LN navigation, but it also usually leads to the leakage of fluorescence and spilled the surgical field [13]. Submucosal administration of ICG helps tumor localization but restrains LN visualization compared to subserosal administration.

CNs is mainly administrated by peritumoral submucosal injection under preoperative gastroscopy. CNs can induce satisfactory tumor localization due to its intuitive black staining effect and rarely brings the contamination of surgical fields. However, submucosal injection of CNs is inferior in lymphangiography because of its limited retention capacity in lymphatic vessels. In addition, the accumulation of CNs in distant LNs is much less than that in peritumoral LNs [14, 15]. Collectively, single tracer (either ICG or CNs) strategy demonstrates unfavorable technical bottlenecks. We notice that the disadvantages of ICG tracer technology can be complemented by the advantages of CNs tracer technology, and vice versa. Consequently, it is promising to implement dual tracers into laparoscopic gastrectomy for a synergistic effect in LN visualization.

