## Methods

### Study design

This is a prospective, unblinded, superiority testing, randomized controlled trial. A parallel group cluster randomized controlled trial with four arms will be conducted. Figure 1 demonstrates the flow chart of current study. Figure 2 contents the schedule of enrolment, interventions, and assessments. Participants were randomized into 4 groups at a 1:1:1:1 ratio: (1) control group: participants will undergo conventional laparoscopic radical gastrectomy without any tracer; (2) ICG group: participants will undergo laparoscopic radical gastrectomy with subserosal ICG navigation; (3) CNs group: participants will undergo laparoscopic radical gastrectomy with submucosal CNs navigation; (4) dual tracer group: participants will undergo laparoscopic radical gastrectomy with both tracers, i.e., subserosal ICG and submucosal CNs. Primary and secondary outcomes will be assessed after the gastrectomy. The study protocol is reported in accordance with the guidelines outlined in the SPIRIT Checklist for Trials (Additional file 1) [16].

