#### Intraoperative lymph node localization and dissection

After anesthesia, ICG (Dandong Yichuang Pharmaceutical Co., Ltd.) powder is diluted into 2.5 mg/ml with saline and then injected into subserosal layer using “hexa-site” method in the ICG group and dual tracer group [18]. Briefly, the injection is performed at 3 sites along the lesser curvature (first branch of left gastric artery, angular and first branch of right gastric artery). Similar injection was repeated along the greater curvature.

A near-infrared (NIR) fluorescence imaging system (PINPOINT, NOVADAQ, Mississauga, ON, Canada) is used to obtain near-infrared fluorescence imaging during surgery. It provides high-definition white light visual field, near-infrared fluorescence visual field, and ICG-specific SPY visual field as well as merged visual field. LN dissection in the ICG group and dual tracer group is performed under the fluorescent laparoscope.

The standard sequence of LN dissection is as follows: (1) total gastrectomy: No. 6 → No. 7, 9, 11p → No. 8a, 12a, 5 → No.1 → No. 4sb → No. 4sa, 11d → No.2; (2) distal subtotal gastrectomy: No. 6 → No. 7, 9, 11p → No. 3, 1 → No. 8a, 12a, 5 → No. 4sb. Selective dissection of No.10 LNs is performed when (1) the primary tumor is located in the middle/upper stomach and invaded a large extent, (2) preoperative radiology suggests splenic lymphadenopathy, (3) significant fluorescent signal of No. 10 LNs, and (4) black stained No. 10 LNs by CNs. Surgical area is routinely inspected for possible residual fluorescent LNs or black-stained LNs, and additional dissection will be performed if necessary. D2 + LN dissection will be performed if fluorescent or black-stained LNs (such as No. 10 or No. 14v) are observed outside D2 region.

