##### Surgical parameters

The following information will be recorded: (1) name of leading surgeon; (2) procedure duration; (3) procedure type especially digestive tract reconstruction method; (4) incision length; (5) whether converted to open surgery and reason; (6) intraoperative blood loss; (7) blood transfusion volume; (8) tumor location; (9) maximum diameter of tumor size; (10) whether distant metastasis is observed and, if any, the location of metastasis; (11) proximal and distal resection margin, radical cure (R0/R1/R2); (12) intraoperative complications including vascular injury, organ injury, tumor rupture, hypercapnia, emphysema, subcutaneous emphysema, air embolism, allergic reactions, etc.; (13) intraoperative death if occurs.

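### Improvement rather than error: the primary lymph node count is assigned an unadjusted t test, where one four-arm model adjusted for pre-randomisation covariates could add precision at almost no cost

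*Protocol article*

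**What the plan says.** All references are to the protocol article.

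- **Outcome:** "The primary outcome is the total number of retrieved LNs". Changes in body weight and in laboratory parameters are among the secondary outcomes.
- **Study design:** "Participants were randomized into 4 groups at a 1:1:1:1 ratio": no tracer, ICG, carbon nanoparticles (CNs), or both.
- **Data analysis:** tests are assigned by type of data, including a t "test for quantitative data, Wilcoxon rank sum test for ranked data". The only multivariable method named is a "Cox regression model for multivariate analysis of survival data". The contrasts between the four arms are not listed.
- **Sample size:** "This study is a superiority testing trial (one-tailed trial"), with a control-group SD of 8.6, a difference of 3 nodes, alpha 0.05 and power 0.8.
- **Intraoperative lymph node localization and dissection:** "The standard sequence of LN dissection is as follows: (1) total gastrectomy", followed by a different list for distal subtotal gastrectomy. Selective No. 10 dissection depends partly on tumour location and partly on tracer signal.
- **Randomization:** the arm follows from the remainder of a random number divided by 4. No strata are used, and surgeons know the allocation before operating.
- **Surgical parameters:** the items recorded include "1) name of leading surgeon; (2) procedure duration; (3) procedure type especially digestive tract reconstruction method" and tumour location, all listed as intraoperative data.

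**The concern.** A two-sample t test leaves all between-patient variation in the error term. Here the protocol itself gives a reason to expect part of that variation to be predictable before surgery. Stations 4sa, 11d and 2 are listed only for total gastrectomy, and the choice between total and distal resection can be expected to follow tumour location. With no stratification, location can also differ between arms by chance. The t test's error rate allows for such imbalance, but the estimate is not corrected for it.

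What is at stake is precision, not bias. Power at the design difference is only about 80% one-sided, and about 70% if the 95% intervals promised in Data analysis are read as two-sided tests. A t test also takes two arms at a time, so each comparison ignores the variance information in the other two. The same reasoning applies to the change outcomes: subtracting baseline uses it, but generally less efficiently than regressing on it.

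**Working it through.** **1. The plan's own figure.** Inputs from Sample size: difference 3, SD 8.6, one-sided alpha 0.05, power 0.80.

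- d = 3/8.6 = 0.349.
- Normal approximation: n = 2 × [(1.645 + 0.842)/0.349]² ≈ 101.6 per arm.
- Noncentral t: n = 102.30 per arm, which matches the printed 102.3, rounded up to 103.
- Dropout: 103/0.8 = 128.75, so 129 per arm and 4 × 129 = 516.

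The design figure is therefore exactly that of a one-sided, unadjusted, two-group t test. This supports reading the t test as the intended primary analysis.

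**2. Effect of adjustment.** If baseline covariates explain a share R² of the variance, the residual SD is 8.6 × √(1 − R²). The pairwise standard error is that SD × √(2/103), and the equivalent unadjusted sample size is 103/(1 − R²). R² is not in the document, so a range is shown. Power is for 3 nodes, 103 per arm, noncentral t.

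| Assumed R² | Residual SD | Pairwise SE | Equivalent n per arm | Power, one-sided | Power, two-sided |
|---|---|---|---|---|---|
| 0 | 8.60 | 1.20 | 103 | 80.2% | 70.3% |
| 0.10 | 8.16 | 1.14 | 114.4 | 83.8% | 74.7% |
| 0.20 | 7.69 | 1.07 | 128.8 | 87.4% | 79.6% |

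**3. Price in degrees of freedom.** With 4 × 103 = 412 analysed, four arm means leave 408 residual degrees of freedom. Location in three levels (assumed) uses 2, and clinical T stage (T1, T2, T3, T4a under the inclusion criteria) uses 3, leaving 403. The loss is negligible.

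**4. Chance imbalance.** Assume 40% of tumours lie in one location. The SD of the difference in proportions between two arms of 103 is √(2 × 0.4 × 0.6/103) = 0.068, so differences up to 1.96 × 0.068 ≈ 13 percentage points lie within the 95% range.

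**5. Which covariates qualify.** A covariate must be fixed before allocation.

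- Clinical T stage qualifies, because eligibility requires it.
- Tumour location qualifies if taken from preoperative endoscopy or imaging, not from the intraoperative record.
- Surgeon qualifies only if assigned before randomisation, because allocation is open to surgeons.
- The procedure performed does not qualify, because it is settled after an open allocation.
- Extra dissection prompted by fluorescence or black staining does not qualify. It is part of how the tracers may raise the count, and adjusting for it would remove part of the effect.

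**6. The 2 × 2 contrast.** The four arms allow dual − ICG − CNs + control to be estimated. Unadjusted SE = 8.6 × √(4/103) = 1.695, so the 95% half-width is 1.96 × 1.695 = 3.32 nodes, against 1.96 × 1.198 = 2.35 for a pairwise contrast. Power for a value of 3 nodes is 55% one-sided and 42% two-sided; 80% one-sided power would need about 204 per arm.

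**The case against.** The strongest reply is that nothing here is wrong. In a randomised trial the unadjusted t test is valid, it agrees with the sample size, and a journal article may leave covariates and contrasts to an analysis plan that is not shown. Its validity stands, which is why this is an improvement and not a fault. The reply does not remove the point, because the article names the test and does not merely stay silent.

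Several stronger readings are tempting and are not supported:

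- A reader might infer that location, procedure and surgeon are known to determine the node count. The document gives no association with the count. The dissection rules make location and procedure plausible; nothing is offered for surgeon or T stage, and Eligibility of surgeons sets an experience threshold without saying how many surgeons take part.
- A reader might infer that simple randomisation leaves the arms unbalanced. It balances them in expectation, and the t test's error rate already covers chance differences.
- A reader might infer that weight and laboratory changes are compared with no regard to baseline. A change score already subtracts it; the argument for ANCOVA is precision.
- A reader might infer that the trial leaves its main hypothesis untested, because the Introduction says "it is promising to implement dual tracers into laparoscopic gastrectomy for a synergistic effect in LN visualization". That is rationale about visualisation. The stated aim is a higher node count, tested as superiority, which purely additive tracer effects could satisfy. No interaction hypothesis is stated.
- Adjustment is not free for every recorded item. Using surgeon or procedure as recorded during surgery could introduce a bias that the t test does not have.

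**Conclusion.** The point holds as a near-costless improvement. At the planned 103 per arm, adjustment would raise one-sided power for 3 nodes from about 80% to about 84% at an assumed R² of 0.10 and about 87% at 0.20; two-sided, from about 70% to about 75% and 80%. At R² = 0 nothing is gained, and only a few degrees of freedom are spent. These figures rest on the control-group SD of 8.6 applying in all arms, on 103 analysed per arm, and on an R² that the document does not supply. That the t tests would be pairwise is inferred from a two-group test in a four-arm trial, since the contrasts are not listed. The 2 × 2 contrast can be estimated but is underpowered, so it is worth reporting at most as a description.

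**What to change.** In Data analysis, replace the t test for the primary outcome with one linear model over all four arms, with robust standard errors. Adjust for tumour location from preoperative endoscopy or imaging and for clinical T stage, and for leading surgeon only if the surgeon is assigned before randomisation. State that neither the procedure performed nor tracer-prompted extra dissection will be a covariate. Report the between-arm contrasts from this model with 95% confidence intervals, and keep the unadjusted t test as a sensitivity analysis.

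For changes in body weight and laboratory values, use ANCOVA with the baseline value as covariate in place of a t test on the change.

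Optionally, report dual − ICG − CNs + control from the same model with its 95% confidence interval, labelled descriptive.

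The cost is a change of analysis wording, about five degrees of freedom, and a case report form entry for tumour location before randomisation. No added patients or visits are needed. The model and its covariates should be fixed in writing before anyone examines outcome data by arm.
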